Expected outcomes: The proposed study will lead to development of a novel rehabilitation protocol for the management of USN in stroke. The protocol may be favorable in reducing the impact of cognitive disability among post-stroke survivors by reducing USN and enhancing the motor and functional recovery.

1. **Background:**

According to the World Health Organization, more than 15 million people experience stroke worldwide each year. Of these, 5 million die and another 5 million gets permanently disabled.[^1^](#_ENREF_1) 70% of strokes occur in low- or middle-income countries (LMICs) such as India. Consequently, the disability burden in LMICs is greater than that of the high-income countries. Further, it has been projected to cause 23 million first-ever strokes, 77 million stroke survivors, and 61 million DALYs by 2030 in LMICs. Thus, the condition has considerable socioeconomic impact on the patients, family members and health care providers, posing a major public health challenge.[^2^](#_ENREF_2) Presently, the stroke incidence in India is much higher than the western developed countries.[^3^](#_ENREF_3)^,^ [^4^](#_ENREF_4) Stroke incidence ranged from 100 to 150/100,000 every year whereas the prevalence is up to 550/100,000 in various states of India.[^5-8^](#_ENREF_5) Due to upward trend in incidence during the last few decades, the disease has now been considered as an epidemic in India.[^7^](#_ENREF_7)^,^ [^9^](#_ENREF_9) Demographic transitions, longevity, and trends of increasing burden in India call for greater attention to rehabilitation services to improve functional outcomes and quality of life among stroke survivors.

Stroke is the most common cause of cognitive and motor impairments. Among the cognitive deficits include a disorder of spatial awareness known as Unilateral Spatial Neglect (USN). USN is a deficit of attention and is described as the inability to report, respond, or orient to sensory or visual stimuli when it appears on the side opposite to the lesion.[^10^](#_ENREF_10) USN is a disorder which can reduce a person’s ability to look, listen or make movements towards one half of their environment. This can also affect their ability to perform many daily functions, such as eating, reading and dressing. Up to 90% of the post-stroke survivors may experience the spatial neglect.[^11^](#_ENREF_11)

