USN is a strong predictor of poor motor recovery and functional performances among the stroke subjects.[^12^](#_ENREF_12) The impaired ability has significant physical, social, and emotional implications. Considering the International Classification of Functioning, Disability and Health, USN undoubtedly affects body structure and function that subsequently leads to activity limitation and participation restriction.

Cognitive rehabilitation has been recommended as one of the important areas of stroke research that warrant independent synthesis of evidence generated in LMICs.[^13^](#_ENREF_13) Further, globally, research on cognitive impairment after stroke is at an earlier stage of evolution than research in motor recovery.[^14^](#_ENREF_14) The studies to enhance cognitive deficits among stroke survivor are recommended as a top first question for research.[^15^](#_ENREF_15) The proposed study may be applicable to the *National Stroke Registry Program (NSRP) / National Programme for Prevention and Control of Cancer, Diabetes, Cardiovascular Diseases and Stroke* (NPCDCS) in terms of rehabilitation services to control and prevent disability for comprehensive management of stroke patients.[^16^](#_ENREF_16)^,^ [^17^](#_ENREF_17)

[^15^](#_ENREF_15)

1. **Literature review:**

USN is a frequent and disabling impairment after stroke. The terms unilateral neglect, visuospatial neglect, hemineglect and spatial neglect are used interchangeably. Although the USN usually occurs on the contralesional side in the right brain damage, the deficit may be observed on the ipsilesional side as well as among subjects with the left brain damage.[^11^](#_ENREF_11)^,^ [^18^](#_ENREF_18)^,^ [^19^](#_ENREF_19) The functional performance of an individual with USN gets hampered. Most of the investigations have been focused on the impairment and management of upper limb functions. In addition to this, the USN affects lower limb functions such as locomotion and stair climbing. The post-stroke subjects with USN are at more risk of falling in comparison to the subjects without USN.[^20^](#_ENREF_20)^,^ [^21^](#_ENREF_21) The functional ambulation including stair climbing gets more impaired than the stroke subjects without USN.[^20^](#_ENREF_20)^,^ [^22^](#_ENREF_22) Further, USN has been identified as a key element that may impede upper limb and lower limb recovery.[^12^](#_ENREF_12)

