**Inclusion Criteria:**

- Age: 20 to 80 years
- Both male & female
- First episode of unilateral stroke (as defined by WHO)
- Ischemic or hemorrhagic stroke
- 1 to 36 months after the stroke onset
- Hemiparesis (right or left) (as assessed by Fugl-Meyer assessment[^38^](#_ENREF_38) upper extremity subsection: 0 to 66)
- USN (defined as an asymmetry between the Letter cancellation task omissions in the contralesional (left) and ipsilesional (right) visual field of at least 2 letters)[^33^](#_ENREF_33)
- Normal visual abilities (with or without glasses)
- Muscle tone: Modified Ashworth scale 1 to 2

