**Intervention:**

*Experimental group:* 40 sessions, 5/week, during 2 months, 1 hour experimental intervention in addition to 1 hour control motor rehabilitation.[^42^](#_ENREF_42)

*Control group Intervention:* Conventional motor rehabilitation (2-hour, 40 sessions).

*Rest Period:* A 10-minute rest period will be provided after 1 hour session to all the study participants. The subjects will be allowed to have water or light snacks during the break.

*Assessment Sessions: 02 pre-, 01 post- intervention and 01 follow-up (1-month)*

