A mirror frame will be positioned vertically on the less-affected side with a therapist standing behind it. The mirror frame will be held parallel to the sagittal plane so that its right edge will be close to the patient’s paretic shoulder. The subject will be asked to turn his head and eyes to look into the center of the mirror so he could clearly see the mirror reflection of the people/ objects that are on the left side. To ensure that the patient is looking in the mirror, the therapist (standing behind the mirror) will enquire about holding of the mirror. A second therapist standing on the patient’s paretic side will hold a block or cone and move towards the subject so that it is well within the reach of the subject’s non-paretic hand but entirely within the neglected (paretic) visual field – about 8 inches below and to the paretic side nose. The therapist will then enquire about the object and ask the patient to reach for the item. Similarly, the objects will be positioned and enquired and asked for the reach and manipulation in different locations. The number of objects, repetition, speed, time and resistance will be considered as parameters for grading the intervention.

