**Outcome measures:**

**Primary measures**

**Unilateral Spatial Neglect**

1. ***Line Bisection Test (LBT)***

There are three 20-cm horizontal black lines in the LBT. One line is on the right of the page, one line is in the center, and one is on the left. The patients will be instructed to mark the center of each line. Errors will be measured in centimeters from the true midline. Leftward errors will be indicated with negative numbers and rightward errors will be indicated with positive numbers. The cutoff score for unilateral visual neglect will be considered as an error of more than 1.4 cm left or right. It is a reliable and valid measure of USN and commonly used measure in stroke studies.[^27^](#_ENREF_27)

1. ***Letter Cancellation Test (LCT)***

A single-target Letter Cancellation Test (LCT) will be the main outcome measure to assess USN requested to cross all O’s on an A4 paper taped on the table and aligned to their sagittal midline. Each paper contained 40 O’s (20 in the contralesional and 20 in the ipsilesional visual field, respectively left and right) and 425 distractor letters. USN has been defined as an asymmetry between the LCT omissions in the contralesional (left) and ipsilesional (right) visual field of at least 2. It also possesses adequate psychometric properties and usually applied in stroke investigations.[^33^](#_ENREF_33)

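### The Letter Cancellation entry rule for neglect fixes contralesional as left and gives no direction, so lesion-side omissions qualify, against the protocol's own definition and therapy target

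*Protocol*

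**What the plan says.** The protocol's Inclusion Criteria define USN by an "asymmetry between the Letter cancellation task omissions in the contralesional (left) and ipsilesional (right) visual field of at least 2 letters". The Letter Cancellation Test (LCT) entry under Primary measures repeats the rule as an "asymmetry between the LCT omissions in the contralesional (left) and ipsilesional (right) visual field of at least 2", and describes the test sheet as carrying "20 in the contralesional and 20 in the ipsilesional visual field, respectively left and right".

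Four other places bear on this rule:

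- The same inclusion list admits "Hemiparesis (right or left") without restriction.
- The Summary and Background describe USN as a failure to respond to a stimulus "when it appears on the side opposite to the lesion".
- The Literature review states that "the deficit may be observed on the ipsilesional side as well as among subjects with the left brain damage".
- In the experimental arm, the upper-limb mirror tasks aim to make action on the lesion side be perceived as action in contralesional space. The parasagittal feedback component places the object "entirely within the neglected (paretic) visual field".

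**The concern.** The rule has two faults, and they compound each other.

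First, contralesional is a property of the patient, not of the page. With a unilateral stroke and right hemiparesis, the contralesional field is the right. The parenthetical labels are wrong for every such patient.

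Second, an asymmetry of at least 2 has a size but no sign. Nothing says that the omissions must be in excess opposite the lesion. Whether a screener works from the printed labels or from the lesion side, a patient with 3 omissions on the lesion side and none on the other meets the rule.

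Such patients lie outside the protocol's own definition of the condition, and the protocol itself says that they occur. The therapy description assumes that the neglected and paretic fields coincide, which is not so for them. At stake is whether the USN comparison, a primary objective, estimates an effect on the condition that the protocol describes, and with the planned power.

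**Working it through.** **1. Applying the rule as written.** The four cases below each have a difference of at least 2.

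| Hemiparesis | Field opposite lesion | Omissions left / right | Meets rule as written? | Deficit opposite lesion? |
|---|---|---|---|---|
| Left | Left | 3 / 0 | Yes | Yes |
| Left | Left | 0 / 3 | Yes | No |
| Right | Right | 0 / 3 | Yes | Yes |
| Right | Right | 3 / 0 | Yes | No |

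Rows 2 and 4 qualify but contradict the Background definition and the therapy target. Equal omissions on the two sides (for example 3 / 3) do not qualify.

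**2. Chance entry when there is no lateral bias.** The 20 targets per field come from the LCT description. The omission rate p per target is not in the documents. I assume p = 5%, 10% or 20%, the same in both fields and independent between targets. With X and Y independent Binomial(20, p), the unsigned rule passes with probability P(|X − Y| ≥ 2) = 1 − P(X = Y) − P(|X − Y| = 1). A signed rule passes with P(X − Y ≥ 2), which by symmetry is half of that.

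| p | P(X = Y) | P(abs. difference = 1) | Unsigned rule | Signed rule |
|---|---|---|---|---|
| 5% | 0.310 | 0.437 | 0.253 | 0.126 |
| 10% | 0.214 | 0.369 | 0.417 | 0.208 |
| 20% | 0.158 | 0.292 | 0.550 | 0.275 |

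These are the chances that one patient without lateral bias passes. They are not the share of such patients among those enrolled, which also depends on who is screened.

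**3. The plan's own sample size.** Box 1 (Sample size section) gives a Line Bisection difference of 8.6, SD 10.6, alpha 0.05, beta 0.1 and 37 per group. I take the test as two-sided, since the sidedness is not stated.

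- Standardised difference: d = 8.6 / 10.6 = 0.811.
- Normal approximation: n = 2 × ((1.960 + 1.282) / 0.811)² = 31.9, so 32 per group. The noncentral t needs 33.
- The stated 37 is therefore not reproduced. It is larger than these inputs require, which leaves some slack.
- Enrolment: 37 × 1.15 = 42.6, so 43 per group, as stated.

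**4. Power scenarios.** Let a fraction f of patients gain nothing, with the SD unchanged. The mean difference becomes 8.6 × (1 − f). Power uses the noncentral t with 2n − 2 degrees of freedom and noncentrality d(1 − f)√(n/2). The value of f is assumed.

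| f | Diluted d | Power, n = 37 | Power, n = 43 |
|---|---|---|---|
| 0 | 0.811 | 93% | 96% |
| 10% | 0.730 | 87% | 92% |
| 20% | 0.649 | 79% | 84% |

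The column for 43 matters because Data Analysis plans intention-to-treat with the last observation carried forward and the dummy tables show 43 per group. It ignores any dilution from the carried-forward values themselves.

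**The case against.** The best defence is that the mix is foreseen. The Literature review recognises ipsilesional deficits and neglect after left brain damage, and Limitations names heterogeneity in the type of deficit, so inclusion could be deliberate. But no passage says so, and none reconciles it with the definition or with therapy that treats neglected and paretic as the same side. The wording conflict remains.

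Several other objections stand and limit the claim:

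- A reader might infer that patients with scattered, non-lateralised omissions qualify as such. They do not. They need a chance difference of 2 or more.
- A reader might infer that lesion-side cases cannot respond, or respond in reverse. The documents give no response data for them. Part of the hour is lower-limb and hand work, and motor recovery is also a primary objective and does not depend on the direction of omissions.
- A reader might join the 25% to 55% figures to the power loss. Nothing links them. The 10% and 20% shares are separate assumptions.
- Box 1 concerns Line Bisection whereas entry is by Letter Cancellation, and no passage ties the direction of omissions at entry to the Line Bisection response.
- Randomisation spreads these patients over both arms, so calling the result biased or uninterpretable would go too far.

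**Conclusion.** The entry rule is wrong as written, in both places where it appears. It mislabels the fields for right-hemiparetic patients and admits omissions on the lesion side, contrary to the protocol's definition of USN and to the stated target of its therapy. That conclusion rests on the text alone and needs no assumption.

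The size of the consequence is uncertain. The expected harm is some loss of power and a less clear reading of the USN comparison. The power figures are scenarios on an assumed share of patients who gain nothing. With 10%, power falls somewhat below the planned 90% if 37 per group are analysed and stays above it with 43. With 20%, it falls below 90% in either case. Chance entry is plausible at moderate omission rates, but its frequency among enrolled patients cannot be derived from the documents.

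**What to change.** In the Inclusion Criteria and in the LCT description, define the two fields by each patient's lesion side and delete the left and right labels. Require that omissions in the field opposite the lesion exceed those in the field on the lesion side by at least 2. If ipsilesional neglect is included on purpose, say so, and reconcile that with the definition of USN and with the upper-limb and parasagittal therapy descriptions.

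The cost is a short amendment, and a few ipsilesional cases become ineligible. The signed rule halves chance entry on the assumptions above (to 13%, 21% and 28%) but does not remove it.

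Requiring the rule to be met twice is not part of this fix. Assessment Sessions lists "02 pre-, 01 post- intervention and 01 follow-up (1-month"), but the SPIRIT schedule has the LCT only once before treatment, at enrolment, so confirmation would need an additional test.

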**Exclusion criteria**:

- Receptive communication or other language disorder (which could interfere with the assessment and treatment process)
- Severe other cognitive impairment (MMSE ≤ 17)[^39^](#_ENREF_39)
- Homonymous Hemianopia.
- Contractures and deformities of hand / finger
- Use of hand splinting or orthosis
- Complex regional pain syndrome
- Concomitant medical illness
- Cardiovascular instability: resting systolic blood pressure >200mmHg and resting diastolic blood pressure >100 mmHg
- Pregnancy
- Renal infection or failure
- Severe depression (Beck depression inventory[^40^](#_ENREF_40)^,^ [^41^](#_ENREF_41) > 30)

**Sample size:**

The power calculation was done using the values *(Box 1)* for USN assessment from a study on mirror therapy for USN.[^27^](#_ENREF_27) Considering the beta = 0.1 and α = 0.05, the calculation inferred that 37 subjects in each group would be sufficient to detect the desired change. However, to compensate possible drop outs (15%), 43 subjects in each group will be enrolled. Thus, the total sample size will be **86**.

*Box 1*

| Study | Primary measure | Values used | Alpha | Beta | Estimated sample size each group | Total sample size |
| --- | --- | --- | --- | --- | --- | --- |
| *Pandian JD et al*[*^27^*](#_ENREF_27) | Line Bisection Test | Mean difference = 8.6  SD = 10.6 | 0.05 | 0.1 | 37 | 74 |

**Group Allocation and Concealment:** The subjects will be randomly allocated between the experimental and control groups in block of 10. The assessor will be unaware about the group allocation of the subjects and will apply the outcome measures both pre- and post intervention. The randomization process will be conducted by an office staff, not associated with the study, using the SPSS Version 23 software. The intervention will be allocated in the ratio of 1:1. The assignment will be serially arranged in sealed opaque envelopes. The subjects will also be blinded to the purpose of the experimental intervention.

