**Data Analysis:**

The data will be analyzed by using IBM SPSS version 23.0. The demographic and baseline features of the study participants will be analyzed in form of mean (SD) / median (IQR) / n (%) and appropriate test [(Mann-Whitney U (U) / independent t (t) / chi-square (χ^2^)] tests will be used to analyze the difference for the characteristics between the groups. For inferential statistics, an intention-to-treat analysis method will be used by carrying forward the last observation. A repeated-measures 2-way ANOVA (continuous data; within factor, time; between factor, group) will be used to study difference for the post intervention and follow-up scores between the groups. The pre-intervention score will be considered as the covariate with group as the independent variable and posttest score as the dependent variable. The significance level will be set at *P*<.05. The dummy tables to represent the findings are provided below -

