|  | Language impairment (writing/reading) - *n (%)* |  |  | χ^2^:p = |

BPL: Below poverty line, LIG: Lower income group, MIG: Middle income group, HIG: Higher income group, UG: Under graduate, PG: Post graduate, BRS-U: Brunnstrom recovery stage of arm, BRS- H: Brunnstrom recovery stage of hand, BRS- L: Brunnstrom recovery stage of lower limb SD: Standard deviation , MAS- Modified ashworth scale, IQR – Inter quartile range, AFO-Ankle foot orthosis, VAS – Visual analog Scale

**Table 2: Changes in Pre- and Post-intervention, and Follow-up scores of the Letter Cancellation Task (LCT) between the experimental and control groups**

| **Outcome measure** | **Pre-intervention** | | **Post-intervention (8-week)** | | **Follow-up (12-week)** | |  | | |
| --- | --- | --- | --- | --- | --- | --- | --- | --- | --- |
|  | **Experimental Group (n=43)** | **Control Group (n=43)** | **Experimental Group (n=43)** | **Control**  **Group (n=43)** | **Experimental Group (n=43)** | **Control**  **Group (n=43)** | **Difference between the means**  **(95% CI)** | **F** | **P value** |
| **LCT (Right)**  *Mean*±*SD*  *Maximum score = 20* |  |  |  |  |  |  |  |  |  |
| **LCT (Left)**  *Mean*±*SD*  *Maximum score = 20* |  |  |  |  |  |  |  |  |  |

n – Number, SD – standard deviation, CI - confidence interval, F – test value ANOVA

**Table 3: Changes in Pre- and Post-intervention, and Follow-up scores of the Line Bisection Test (LBT) between the experimental and control groups**

| **Outcome measure** | **Pre-intervention** | | **Post-intervention (8-week)** | | **Follow-up (12-week)** | |  | | |
| --- | --- | --- | --- | --- | --- | --- | --- | --- | --- |
|  | **Experimental Group (n=43)** | **Control Group (n=43)** | **Experimental Group (n=43)** | **Control**  **Group (n=43)** | **Experimental Group (n=43)** | **Control**  **Group (n=43)** | **Difference between the means**  **(95% CI)** | **F** | **P value** |
| **LBT (Right)**  *Mean*±*SD*  *Maximum score = 20* |  |  |  |  |  |  |  |  |  |

n – Number, SD – standard deviation, CI - confidence interval, F – test value ANOVA

**Table 4: Changes in Pre- and Post-intervention, and Follow-up scores of the Fugl-Meyer Assessment (FMA) between the experimental and control groups**

| **Outcome measure** | **Pre-intervention** | | **Post-intervention (8-week)** | | **Follow-up (12-week)** | |  | | |
| --- | --- | --- | --- | --- | --- | --- | --- | --- | --- |

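### The 37 per group in the sample-size section does not follow from its own inputs (33 is enough), and Box 1's difference and SD have no unit or Line Bisection score attached

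*Protocol*

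**What the plan says.** The sample-size section of the protocol bases the calculation on the Line Bisection Test (LBT), using values from a published trial of mirror therapy in neglect. Box 1 gives "Mean difference = 8.6" and an SD of 10.6, neither with a unit. The error rates are given as "Considering the beta = 0.1 and α = 0.05", and the result is that "the calculation inferred that 37 subjects in each group would be sufficient to detect the desired change". For 15% dropout this becomes 43 per group, 86 in total. On allocation the text says that "The intervention will be allocated in the ratio of 1:1". Neither the test nor its sidedness is named. The Data Analysis section says only that "The significance level will be set at *P*<.05".

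The LBT is described under the primary measures: "There are three 20-cm horizontal black lines in the LBT", and "Errors will be measured in centimeters from the true midline". Leftward errors are negative and rightward errors positive. No rule says how the three lines become one score. Dummy Table 3, which is to report the LBT, carries the label "Maximum score = 20".

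**The concern.** Two things do not fit. First, a standardised difference of about 0.81 at 90% power ordinarily needs slightly more than 30 per group, so 37 looks too high. Second, a mark on a 20-cm line lies at most 10 cm from its midpoint, so an SD of 10.6 is larger than a centimetre error on one line, or averaged over lines, can have.

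What is at stake is whether the calculation can be checked and read. A sample size that its own inputs do not reproduce cannot be verified. If the target difference has no defined scale, the observed LBT result cannot be compared with the effect for which the trial was planned.

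**Working it through.** **Inputs.** From the sample-size section and Box 1: difference 8.6, SD 10.6, alpha 0.05, beta 0.1, allocation 1:1, dropout 15%. Assumption: a two-sided test, because sidedness is not stated. From the LBT description: three 20-cm lines, signed error in cm.

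**1. Trying to reproduce 37.**
- Standardised difference: d = 8.6 / 10.6 = 0.811; d² = 0.658.
- Normal approximation: n = 2(1.960 + 1.282)² / d² = 2 × 10.51 / 0.658 = 31.9, so 32 per group.
- Two-sample t-test (noncentral t): n = 32.9, so 33 per group.

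Other conventional settings also miss 37:

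| Setting | n per group (normal / t) |
| --- | --- |
| Two-sided, 80% power | 24 / 25 |
| Two-sided, 90% power | 32 / 33 |
| Two-sided, 95% power | 40 / 41 |
| One-sided, 90% power | 27 / 27 |
| One-sided, 95% power | 33 / 34 |

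The number 37 can be reached only with something the protocol does not state. Examples are a difference of 8.0 instead of 8.6 (normal approximation, 37), a worst-case rank-test efficiency of 0.864 (31.93 / 0.864 = 36.96), or a dropout allowance already added once (32 × 1.15 = 36.8).

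**2. Power at the stated numbers** (t-test, d = 0.811, two-sided 0.05).
- 37 per group: 93.1%
- 36 per group: 92.4%
- 43 per group: 96.1%

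**3. Dropout.**
- 37 × 1.15 = 42.55, so 43: the protocol's figure.
- 37 / (1 − 0.15) = 43.53, so 44: the number that leaves 37 after a 15% loss.
- 43 × 0.85 = 36.55: the expected number completing, about 36.
- From the reproduced requirement: 32 / 0.85 = 37.6 and 33 / 0.85 = 38.8, so 38 to 39 per group, or 76 to 78 in total, against 86 planned.

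**4. Scale of the LBT.** A variable confined to −10 to +10 has its largest SD when half the values sit at each end. That SD is 10, or about 10.1 as a sample SD with 37 values and 10.2 with 24. The possible readings of Box 1 are:

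| Reading of 8.6 and 10.6 | Range of the score | Can the SD be 10.6? | Target in cm |
| --- | --- | --- | --- |
| cm, one line or mean of three | −10 to +10 | No | – |
| cm, sum of three lines | −30 to +30 | Yes | 8.6 / 3 = 2.9 per line |
| cm, change in a one-line or mean score | −20 to +20 | Yes | 8.6 |
| mm, one line or mean of three | −100 to +100 mm | Yes | 0.86 |

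The protocol states none of the three feasible readings. They put the target anywhere from 0.86 to 8.6 cm per line.

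**5. Table 3.** A maximum of 20 matches neither the 10 cm limit for one line nor the 30 cm limit for a sum.

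**The case against.** The strongest reply is that nothing in the conduct of the trial changes. Only the ratio 8.6 / 10.6 enters the formula, so a pure change of unit leaves the required n where it is. The miscount runs in the safe direction, and the dropout slip is one participant per group. The figure of 37 might also come from a rank-test allowance that the authors did not mention. All of this stands as to the number enrolled. It does not make 37 follow from what is written, and it does not say what 8.6 means on the trial's own scale.

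Three stronger readings are tempting, and the documents support none of them.
- A reader might infer that the trial is under-powered. On the stated ratio it is larger than it needs to be, even after a 15% loss.
- A reader might infer that an SD of 10.6 is simply impossible. That holds for a centimetre score on one line or the mean of three. Because no combination rule is given, and Box 1 does not say whether its SD refers to scores or to change, a sum or a change score remains possible.
- A reader might set the target against the 1.4 cm neglect cut-off. That is a threshold for classifying an individual patient; a difference between group means need not exceed it.

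Table 3's label is identical to the one for letter cancellation in Table 2, where 20 targets per side make it correct. A copied label is the likeliest explanation, so it is an editorial slip and weak evidence about the intended scale.

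**Conclusion.** The point holds and should be fixed, but it does not threaten the trial. On Box 1's inputs, and assuming a two-sided two-sample comparison, the requirement is 33 per group (32 by normal approximation). The stated 37 is 4 to 5 per group too high and corresponds to about 93% power, not 90%. Separately, Box 1's difference and SD cannot be placed on the LBT scale for a single-line or mean score, and the readings that would make them feasible are not stated. The standardised target of 0.81 is therefore fixed, while the raw target is undefined. The dropout step (43 where 44 would preserve 37) and the Table 3 maximum are minor. The unit used in the source trial cannot be checked from the protocol.

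**What to change.** Keep 86 enrolled and change the text.
- **Sample size.** State that 33 per group give 90% power for a standardised difference of 0.81 (two-sample t-test, two-sided alpha 0.05), and that 43 randomised per group, about 36 evaluable after a 15% loss, give about 92%. Alternatively, name the test, sidedness and any allowance that yield 37, and state the dropout formula; with 37 as the requirement, dividing by 0.85 gives 44.
- **Box 1.** Check the unit and type of score in the source trial. Then restate the difference and SD in the unit, and under the line-combination rule, by which this trial will score the LBT, and say whether they refer to scores or to change. The protocol does not yet fix that rule, so the investigators need to choose it and write it into the LBT description, preferably before any outcome data are examined.
- **Table 3.** Replace the maximum with the range of the chosen score.

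The cost is a rewritten sample-size paragraph, an added sentence in the LBT description and one table label. Enrolment, procedures and duration do not change.

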**Hypothesis:**

1. Task-based and Magnified Mirror therapy protocol for the paretic upper limb provided for 2 months will decrease the Unilateral spatial neglect by 50% in 1 to 36 months post stroke subjects with hemiparesis when compared with the conventional management.
2. Task-based and Magnified Mirror therapy protocol for the paretic upper limb provided for 2 months will enhance the motor recovery by 30% in 1 to 36 months post stroke subjects with hemiparesis when compared with the conventional management.

**Design***:* Randomized controlled, single blinded trial

**Setting:** Neuro-Rehab Laboratory*,* Department of Occupational Therapy, Pt. Deendayal Upadhyaya National Institute for Persons with Physical Disabilities, New Delhi

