**Data Collection:**

The data will be collected using the assessment proforma provided as ***Annexure I.*** The proforma comprises items/questions related to demographic aspects of the subjects such as age, gender, type of stroke, duration of stroke, area of involvement, functional performance. Additionally, the clinical evaluation of a standard neuro-rehabilitation condition will also be covered. All the standardized outcome measures in form of data collecting tool have been provided in the ***Annexure II to VII.***

The flow of study process and schedule of enrolment, intervention, and assessment (SPIRIT guidelines[^55^](#_ENREF_55)) are provided below –

Post- stroke patients (1 to 36 months) – Screened for the eligibility (n=….)

Block Randomization (n=86)

Conventional Rehabilitation –

4 weeks

Experimental intervention (n=43)

(Task-based & Magnified Mirror Therapy) + Conventional Rehabilitation

40 sessions, 2 hours each during 8 weeks

Control Intervention (n=43)

(Conventional Rehabilitation)

Dose matched for duration

40 sessions, 2 hours each during 8 weeks

Enrolment

Allocation

Follow-up

Post intervention Assessment (T2)

Baseline Assessment (T1)

Follow up Assessment (T3)

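### The single block size of 10 stated in the protocol would let a person who tracks assignments deduce, on average, about 13 of the 86 allocations

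*Protocol*

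**What the plan says.** The paragraph on Group Allocation and Concealment states that subjects are "randomly allocated between the experimental and control groups in block of 10" and that "The intervention will be allocated in the ratio of 1:1". It names no other block size and no stratification factor. Under Setting, the protocol names one department's laboratory. The study flow diagram repeats block randomisation of 86 subjects, so one list runs through the whole trial.

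Two safeguards are given. An office staff member outside the study runs the randomisation, and "The assignment will be serially arranged in sealed opaque envelopes". On masking, the design is a "Randomized controlled, single blinded trial". "The assessor will be unaware about the group allocation of the subjects", and subjects are blinded only to the purpose of the experimental intervention.

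The protocol does not mention masking of therapists. The sections on the experimental and control interventions describe visibly different programmes: mirror boxes, a magnifying mirror and a parasagittal mirror in one arm, and conventional rehabilitation with attention and scanning activities in the other.

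The protocol does not say who enrols subjects, who opens the envelopes, or whether the block size is kept from these people.

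**The concern.** Envelopes and an independent list-maker hide the content of the next card. They do not stop anyone from working it out from the cards already opened. In a 1:1 block of 10, once five subjects have gone to one arm, every remaining place in that block belongs to the other. A person needs two things for this: the block size, which is in the protocol, and the earlier assignments in the block, which staff treating both arms at one site could come to know.

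If such a person also influenced enrolment, some subjects could be admitted, deferred or turned away with the next arm in mind. The protocol leaves some room for that. Concomitant medical illness is an exclusion without a definition, the language criterion depends on a judgement of interference, and the window of 1 to 36 months after stroke allows most subjects to wait without losing eligibility. Selection of this kind takes place before assessment, so a masked assessor does not correct it.

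**Working it through.** The protocol gives no predictability figure, so there is none to reproduce first.

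**Inputs.** Block size 10, ratio 1:1 (5 + 5 per block) and 86 subjects, from Group Allocation and Concealment, Sample size and the study flow diagram. One list, because there is one site and no stratification. 86 = 8 × 10 + 6, so there are eight full blocks and six places of a ninth.

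**Certain allocations per full block.** An allocation is certain when one arm of the block is already full. This is the length of the run of identical assignments that ends the block. For a block of 2m:

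E = 2m / (m + 1); with m = 5, E = 10 / 6 = 1.667.

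Check by direct count: 2 × [C(9,5) + C(8,5) + C(7,5) + C(6,5) + C(5,5)] / C(10,5) = 2 × (126 + 56 + 21 + 6 + 1) / 252 = 420 / 252 = 1.667.

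**The part-block.** Among six places, only the sixth can be certain, and only if the first five are all in one arm: 2 / C(10,5) = 2 / 252 = 0.008.

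**Total.** 8 × 1.667 + 0.008 = 13.34 of 86, or 15.5%. In 50,000 simulated lists the mean was 13.33 and the central 95% range 9 to 19. The count is never below 8, because the last place of each full block is always determined.

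**Best guess over all places.** If one always guesses the arm with more places left, the expected number of correct guesses in a full block is m + 2^(2m−1) / C(2m,m) − 0.5 = 5 + 512 / 252 − 0.5 = 6.53. Exact recursion over all 86 places gives 55.7 correct (64.8%), against 43 (50%) by chance.

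**Alternatives.** Fixed sizes were computed exactly. Varied sizes were simulated (3,000 lists each), with sizes drawn equally often, the list cut at 86, and an observer who knows the set of sizes and all earlier assignments but not the order of sizes.

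| Blocks | Certain allocations of 86 | Best guess correct |
|---|---|---|
| Fixed 4 | 28.0 | 71% |
| Fixed 6 | 21.0 | 68% |
| Fixed 8 | 16.2 | 66% |
| Fixed 10 (protocol) | 13.3 | 65% |
| Varied 4, 6, 8 | 2.0 | 68% |
| Varied 6, 8, 10 | 1.4 | 66% |
| Varied 8, 10, 12 | 1.1 | 65% |

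The weakness is that the size is fixed and disclosed, not that it is 10; smaller fixed blocks are worse. Varying the sizes removes most of the certainty but does not reduce guessing in general.

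**The case against.** The strongest reply is that the figure of 13 describes a perfectly informed observer whom the protocol does not place anywhere. No section says that those who treat also enrol, or that any one person sees the whole sequence. One experimental component alone uses two therapists. Even their knowledge of the arm is inferred from single blinding and the nature of the therapy. Nothing indicates that the protocol is released publicly before enrolment; the sections on registration and dissemination speak of a registry entry and of the findings. All of this stands, and it makes the figure conditional.

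Existing safeguards also count. The list is made outside the study and the envelopes are sound. Several eligibility criteria are numeric. The letter cancellation test, which defines neglect for entry, is also an outcome measure, so it may well be in the masked assessor's hands. The Data Analysis section plans the pre-intervention score as a covariate, which would adjust for selection on that measured score. It would not adjust for unmeasured prognosis, and none of these safeguards governs when a subject is enrolled.

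Finally, the remedy is partial: an enroller acting on a 65% guess would be no worse off under varied blocks. That is correct. The gain is confined to the allocations that could otherwise be known with certainty.

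A reader might also infer that 86 not being a multiple of 10 harms the planned 43 per arm. It does not matter: the last six places split at worst 5:1, giving 45:41, and 44:42 or closer has probability 200 / 210 = 0.95.

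**Conclusion.** The point holds as an avoidable weakness in concealment. With one stated block size of 10, one department and no stratification, about 13 of 86 allocations (15.5%; 95% range 9 to 19, minimum 8) are deducible by a person who knows the block size and every earlier assignment in the block. The count is an expectation and rests on that full knowledge.

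A reader might infer that staff will foresee these allocations, or that the trial will be biased. The protocol supports neither: it does not say that enrolling staff treat subjects or follow the sequence. What can be said is that it describes no separation of roles, and no withholding of the block size, that would close the route. The section contains no contradiction or wrong figure. The case for changing it is that the improvement is almost free.

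**What to change.** The same independent office staff member should generate the list with randomly varied, fairly large block sizes, for example 8, 10 and 12, and should alone hold the sizes and their order. The stated size should come out of the protocol, which would say only that permuted blocks of varying, undisclosed size are used. Small blocks such as 4, 6 and 8 should be avoided, because they raise the best-guess rate to about 68%.

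The sizes need not be forced to sum to 86. If they were, with 43 per arm printed in the protocol, the final allocation would be certain to anyone who had followed the whole list.

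The effect is a fall in certain allocations from about 13 to about 1 for an observer who knows the set of sizes. The best-guess rate of about 65% does not fall. The cost is a new list and one sentence of protocol text, with no change to sample size, visits or analysis. A further sentence naming who enrols subjects and who opens the envelopes would show whether the route exists at all.
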